##### PSCI incidence

In accordance with the 2023 AHA/ASA scientific statement (5), PSCI will be defined as a MoCA score <26 at the 3-month post-stroke evaluation. PSCI incidence will be calculated as the number of confirmed cases/total number of enrolled participants.

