### Diagnostic criteria

Ischemic stroke will be diagnosed according to the 2019 American Heart Association/American Stroke Association (AHA/ASA) Guidelines (20) and the Chinese Guidelines for Acute Ischemic Stroke (2023) (21). Cognitive impairment will be established with reference to the 2023 AHA/ASA scientific statement *“*Cognitive Impairment After Ischemic and Hemorrhagic Stroke*”* (5) as a Montreal Cognitive Assessment (MoCA) score below 26.

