#### Inclusion criteria

Inclusion criteria include:

Meets both stroke and cognitive impairment definitions;Aged 18–75 years, either of sex;Ischemic stroke onset 7–30 days before enrolment;MoCA < 26 and able to cooperate with acupuncture and assessments;Stable vital signs;National Institutes of Health Stroke Scale (NIHSS) score 1–15;Written informed consent from the patient or legal guardian.

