#### Exclusion criteria

Exclusion criteria include:

Unstable vital signs or uncontrolled severe cardiopulmonary disease;Previous stroke;Pre-existing cognitive impairment, depression, or other psychiatric disorders;Malignancy, significant hematological disorder, respiratory failure, or active infection;Severe dysfunction of other organs or critical systemic diseases;Severe visual/hearing impairments or aphasia precluding cooperation;Imaging subgroup only: MRI contraindications (metallic implants/electronic devices) or left-handedness.

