### Outcome measures

#### Primary outcome measurement

The primary outcome is the change in MoCA scores from baseline to the end of the 4-week treatment period. This time point corresponds to completion of the EA course and the early subacute rehabilitation phase, when treatment intensity and neuroplastic potential are highest and short-term clinical decision-making is often made. MoCA is a validated screening tool for global cognitive function, covering seven domains: visuospatial/executive function, naming, attention, language, abstraction, delayed recall, and orientation (total score = 30). Using the standardized cutoff of <26 established for cognitive impairment detection, lower scores denote greater severity of cognitive dysfunction (29). To address longer-term clinical relevance, MoCA will also be reassessed at 3 months after stroke onset, and PSCI incidence at 3 months will be analyzed as a key secondary outcome.

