Continuous variables will be presented as mean ± standard deviation (SD) when normally distributed or median with an interquartile range (IQR) for non-normally distributed data. Between-group comparisons will utilize independent samples t-tests for normally distributed variables and Mann–Whitney U-tests otherwise. Within-group pre-post comparisons will use the Wilcoxon signed-rank test. Correlation analyses will preferentially apply Pearson’s method; if either variable violates normality, Spearman’s rank correlation will be substituted. To control for confounders, covariates including age, sex, education level, stroke severity (baseline NIHSS score), and time from stroke onset to enrolment will be incorporated into multivariable linear regression models to evaluate between-group differences in the primary endpoint and key secondary cognitive outcomes. Where available, additional vascular and imaging-related factors, such as stroke subtype, lesion side, and vascular territory, lesion volume, baseline white matter hyperintensity burden (e.g., Fazekas score), receipt of intravenous thrombolysis, and major vascular comorbidities, will be explored as candidate covariates in sensitivity analyses.

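### The outcome called PSCI incidence counts persistence of an impairment that every participant has at entry, so it cannot estimate incidence or prevention of PSCI

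*Protocol article*

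**What the plan says.** All references are to the protocol article.

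- **Entry.** Under Diagnostic criteria, cognitive impairment is defined "as a Montreal Cognitive Assessment (MoCA) score below 26". Inclusion criteria require "MoCA < 26 and able to cooperate with acupuncture and assessments", with "Ischemic stroke onset 7–30 days before enrolment". No lower MoCA limit is set. Exclusion criteria remove "Pre-existing cognitive impairment, depression, or other psychiatric disorders".
- **Outcome.** Under PSCI incidence, "PSCI will be defined as a MoCA score <26 at the 3-month post-stroke evaluation", and "PSCI incidence will be calculated as the number of confirmed cases/total number of enrolled participants".
- **Status.** Primary outcome measurement states that "PSCI incidence at 3 months will be analyzed as a key secondary outcome". The same section has MoCA itself reassessed at 3 months. Innovation and limitations lists both the 3-month MoCA and PSCI incidence as key secondary outcomes.
- **Analysis.** Clinical data analysis names "covariates including age, sex, education level, stroke severity (baseline NIHSS score), and time from stroke onset to enrolment" for the adjusted models of the primary endpoint and key secondary cognitive outcomes. Baseline MoCA is not named. The same section treats the secondary outcomes, PSCI incidence among them, as exploratory, with descriptive p-values.

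**The concern.** Incidence is the rate of new cases among people who do not yet have the condition. Here the entry criterion and the outcome use the same instrument and the same cut-off. The entry score is already post-stroke, and impairment that predates the stroke is excluded. A participant whose MoCA does not change at all is counted as an incident case, and the measure can improve only through recovery to 26 or more.

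Two things are at stake. First, a lower proportion in the EA arm, reported under the present label, would say that EA lowers the incidence of PSCI. A reader would take that as prevention, which this population cannot show. Second, the outcome responds unevenly across the entry range. Someone who enters at 25 leaves the case group after a 1-point rise, while someone who goes from 12 to 24 stays in it. Baseline MoCA is thus likely to be a strong predictor of the outcome, yet it is missing from the named covariates.

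**Working it through.** **1. Definitions side by side (no assumption needed).**

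| | Entry | Outcome |
|---|---|---|
| Instrument | MoCA | MoCA |
| Cut-off | <26 | <26 |
| Time | 7–30 days after onset | 3 months after onset |
| Who | all participants | all enrolled (denominator) |

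Participants meeting the case definition at baseline: 72 of 72. Participants at risk of a new case: 72 − 72 = 0. Among those assessed, the proportion below 26 equals 1 − the proportion at 26 or more, which is persistence. The article gives no expected rate, effect or power for this outcome, so there is no figure of its own to reproduce.

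**2. Dependence on the entry score (illustrative).** The article gives no MoCA mean, SD or retest error, so these are assumptions. Let the change to 3 months be normal with mean m = 2 or 3 points and SD 3. For entry score b,

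P(still <26 | b) = Φ((25.5 − b − m)/3).

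- b = 25: Φ(−1.5/3) = 0.31 for m = 2; Φ(−2.5/3) = 0.20 for m = 3.
- b = 20: Φ(3.5/3) = 0.88; Φ(2.5/3) = 0.80.
- b = 16: Φ(7.5/3) = 0.99; Φ(6.5/3) = 0.98.

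**3. Who supplies the recoveries.** This is a simulation with 1,000,000 patients per setting. The true score is normal with mean 19 (SD 4.5) or 21 (SD 4). Baseline and 3-month scores carry independent errors of SD 1, 1.5 or 2, are rounded and bounded to 0–30, and patients are kept if the observed baseline is below 26.

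- Participants entering at 23–25 make up about 16–26% of the sample, which is about 6–9 of 36 per arm.
- With no true change, 29–31% of those entering at 25 score 26 or more at follow-up, against 0–2% or so at 20 and about 0% at 15.
- With +2 points in everyone, the figures are 57–81% at 25, 1–11% at 20 and about 0% at 15. Entrants at 23–25 supply 61–87% of all recoveries.
- With +4 points in everyone, that share falls to about 48–64%.
- Overall recovery with +2 points is about 10–19%: 0.10 × 72 ≈ 7 to 0.19 × 72 ≈ 14 participants.

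**4. Who supplies the treatment contrast.** Same simulation, control +2 and EA +4, taking recoveries at +4 minus recoveries at +2. Entrants at 23–25 supply about 35–46% of the between-arm difference. This depends on the assumed background gain: with control 0 and EA +2, the same calculation gives about 53–85%.

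The model in step 2 was also applied with baseline mean/SD of 18/4, 20/4 or 22/3 and a 2-point EA benefit. There the wider band 22–25 (17–51% of the sample) supplies 59–82% of control recoveries and 29–61% of the between-arm difference.

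**The case against.** **The article separates the two states.** It calls the entry state IS-CI and reserves PSCI for the 3-month evaluation, so each participant is first classified as PSCI or not at 3 months. The definition and formula are stated openly, and comparing the proportions by arm is a valid randomized contrast. All of that stands, except that a different name for the entry state does not alter what is counted: same instrument, same threshold, nobody above it at the start.

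**Safeguards exist.** The outcome is exploratory with descriptive p-values. The primary endpoint is a MoCA change score, and MoCA is scored again at 3 months, so a rise from 12 to 24 is not lost to the trial. The article nowhere claims that EA prevents PSCI; its stated aim is to improve cognition in patients already impaired. This stands and limits the harm. It does not correct the label.

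**Stronger readings that a reader might infer.** One is that the result is decided largely by patients entering just below 26. The documents do not support this. They give no baseline distribution, and the high share in step 3 concerns recoveries, not the treatment contrast. Another is that a chance excess of near-threshold patients in one arm biases the comparison. It does not: randomization balances this in expectation and the confidence interval reflects it. The case for adjustment is precision and protection against chance imbalance.

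**Covariates may be settled elsewhere.** The named list is introduced as non-exhaustive, and the model for a binary secondary outcome may be set in an analysis plan not shown. That is fair, so the missing covariate is the lesser part of this point.

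**Conclusion.** The definitional part is certain and follows from the article alone: 0 of 72 participants are at risk of a new case, so the outcome measures persistence of impairment, and the trial cannot estimate incidence or prevention of PSCI. Following the plan as written would report persistence under the name of incidence.

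The dependence on the entry score is clear in direction but rests on assumed MoCA distributions, retest error and recovery. With a 2-point gain, entrants at 23–25 supply most recoveries. They supply under half of the between-arm difference if controls gain 2 points and EA adds 2 more, and a larger share if controls gain nothing. That supports including baseline MoCA; it does not support calling the comparison invalid. The primary endpoint is unaffected.

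**What to change.** - Rename the outcome persistence of cognitive impairment at 3 months, or its complement, recovery to MoCA ≥26, in the abstract, Figure 1, Table 1, the outcome sections, the analysis section and the limitations.
- State that every participant meets the criterion at entry, so the outcome measures neither incidence nor prevention of PSCI.
- Include baseline MoCA in the between-arm comparison of this outcome.
- Report it beside the continuous 3-month MoCA, which is already collected.
- If recovery is tabulated by baseline MoCA (for example 23–25 against ≤22), label the table descriptive.

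**Cost.** Wording, plus one covariate already measured in everyone; no new visits, data or participants. The new label no longer supports a prevention claim. With about 7–14 recoveries in 72 under the +2 scenario, the adjusted estimate will be imprecise, and cells split by arm and baseline score will be very small.

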## Methods

### Research design

This single-blind, RCT will be conducted in the Department of Rehabilitation Medicine, West China Hospital of Sichuan University (Chengdu, China). A total of 72 inpatients with IS-CI will be randomized 1:1 to receive EA or sham electroacupuncture (sEA). Figure 1 outlines the study flow, and Table 1 details the schedule of enrolment, interventions, and assessments.

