### Sample size

This exploratory trial was primarily designed to estimate effect sizes and assess protocol feasibility. Consistent with pilot-trial recommendations for acupuncture and traditional Chinese medicine (22, 23), we set the target sample size at 30 participants per arm. Allowing for an anticipated 20% attrition, we therefore planned to enroll 36 participants in each group (total *n* = 72). For the MRI substudy, we will randomly select 15 participants per arm (*n* = 30) from the clinical cohorts, in line with Desmond and Glover’s guidance on imaging sample sizes (24). Under a two-tailed *α* = 0.05, this total sample provides approximately 80% power to detect medium-to-large correlations (r ≥ 0.50) between QSM-derived susceptibility measures and cognitive outcomes, based on Fisher’s z transformation in G*Power 3.1. Smaller associations will be interpreted with caution, and the MRI substudy is therefore primarily intended to provide preliminary estimates of effect sizes and variance components to guide the design of future, adequately powered imaging trials. With 15 participants per arm, the substudy will also have approximately 80% power to detect between-group differences in 4-week changes in regional susceptibility of approximately 0.8 standard deviations (Cohen’s d), whereas smaller treatment effects on QSM will be treated as exploratory and described descriptively.

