#### Assessment timepoints

The primary outcome (MoCA) and most secondary outcomes (MMSE, MBI, HAMA, HAMD, and PSQI) will be assessed twice: at baseline and at the end of the 4-week treatment period. PSCI incidence, defined based on MoCA <26, will be assessed once at 3 months after stroke onset.

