### Clinical data analysis

Statistical analyses will be performed using IBM SPSS 26.0 (IBM, Armonk, NY, USA). The primary efficacy analyses will follow the intention-to-treat (ITT) principle (35), including all randomized participants analyzed according to their allocated group, irrespective of treatment adherence. A per-protocol (PP) population will be defined as participants who complete at least 16 of the 20 planned treatment sessions (≥80% adherence) and have the primary endpoint (week-4 MoCA) assessed. For the MRI substudy, the PP set will include participants with analyzable QSM data at both baseline and week 4.

MoCA change from baseline to week 4 will be the sole primary endpoint, and hypothesis testing for this outcome will use a two-sided significance level of 0.05. Prespecified secondary clinical outcomes (MMSE, MBI, HAMA, HAMD, PSQI, and PSCI incidence) will be analyzed without formal adjustment for multiplicity and will be interpreted as exploratory. For these endpoints, we will report effect sizes with 95% confidence intervals and regard *p*-values as descriptive, in order to avoid over-interpretation of nominal statistical significance in this pilot trial. Multiplicity for imaging analyses across QSM regions of interest will be controlled using false-discovery-rate correction as described below.

For the primary endpoint (change in MoCA from baseline to week 4), if missing data at week 4 exceeds 5% of randomized participants, multiple imputation under a missing-at-random assumption will be used as the main ITT analysis (36, 37). For secondary outcomes, analyses will primarily use available cases, and sensitivity analyses with multiple imputation may be conducted if missingness is substantial. Reasons for missing data will be documented wherever possible.

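### The PSCI incidence formula keeps participants with no 3-month MoCA in the denominator, in effect counting them as PSCI-free, and conflicts with the available-case rule for secondary outcomes

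*Protocol article*

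**What the plan says.** The PSCI incidence section (Secondary outcomes) gives both the case definition and the formula. The definition is that "PSCI will be defined as a MoCA score <26 at the 3-month post-stroke evaluation"; the formula is that "PSCI incidence will be calculated as the number of confirmed cases/total number of enrolled participants". The Assessment timepoints section adds that "PSCI incidence, defined based on MoCA <26, will be assessed once at 3 months after stroke onset", so there is one opportunity to be classified.

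The Clinical data analysis section lists PSCI incidence among the secondary clinical outcomes and sets a general missing-data rule: "For secondary outcomes, analyses will primarily use available cases". Multiple imputation is a firm commitment only for the week-4 primary endpoint; for secondary outcomes it is an optional sensitivity analysis. The same section treats these outcomes as exploratory and their p-values as descriptive.

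Two other statements matter. The Inclusion criteria require "MoCA < 26 and able to cooperate with acupuncture and assessments", so every participant is below the PSCI cutoff at entry. The Sample size section expects loss: "Allowing for an anticipated 20% attrition, we therefore planned to enroll 36 participants in each group".

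**The concern.** A case can be confirmed only by a 3-month MoCA. Someone who misses that visit is excluded from the numerator by definition and retained in the denominator by the formula, which is arithmetically the same as scoring that person 26 or above. For participants who were all below 26 at baseline, this is the most favourable value that could be assigned.

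Two consequences follow. Loss to follow-up lowers the reported PSCI rate in whichever arm it occurs, so equal loss understates both rates and dilutes a true difference, while unequal loss creates a difference in favour of the arm that lost more. Second, the plan contains two rules that give different answers whenever anyone is lost, so the analyst must choose between them.

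Unequal loss is plausible, though not certain. The Withdrawal criteria remove participants for poor adherence and for serious adverse events requiring discontinuation. The arms also differ physically: deeper needling with deqi and 1–2 mA current in one, superficial needling without current in the other. If a withdrawn participant has no 3-month MoCA, a withdrawal would count as a cognitive success. The article calls this a key secondary outcome and relies on it, with the 3-month MoCA, for longer-term relevance.

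**Working it through.** **Inputs from the article.** 30 participants per arm targeted, 20% attrition, 36 per arm enrolled (Sample size); case = MoCA below 26 at 3 months; denominator = all enrolled (PSCI incidence).

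**Assumptions, not in the article.** The true 3-month PSCI rate p in this population; how loss splits between the arms; that the 20% attrition applies to the 3-month visit; and that loss is unrelated to PSCI status. The article gives no planning rate or power for PSCI incidence, so there is no stated PSCI figure to reproduce.

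**The plan's own figure.** 30 × (1 + 0.20) = 36 per arm, which matches the stated denominator.

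**Formula.** With loss d in an arm of n, the expected number of confirmed cases is n × (1 − d) × p. Dividing by n gives a reported rate of p × (1 − d).

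**Equal loss of 20% in both arms.**
- Assumed p = 60%: 0.60 × 0.80 = 48%.
- At the two prevalences quoted in the Introduction (illustration only): 0.44 × 0.80 = 35.2%; 0.531 × 0.80 = 42.5%.
- Assumed true rates of 50% and 70%: reported 40% and 56%, so a 20-point difference becomes 16.
- With no true effect, the spurious difference is 0.

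**Unequal loss, no true effect.** Spurious difference = p × (d₁ − d₂), in favour of the arm with more loss. At an assumed p = 60%:

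| Imbalance in loss | Spurious difference |
|---|---|
| 0 points | 0 |
| 5 points | 0.60 × 0.05 = 3 points |
| 10 points | 0.60 × 0.10 = 6 points |
| 20 points (e.g. 30% vs 10%) | 0.42 vs 0.54 = 12 points |

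For the 20-point imbalance, other assumed true rates give 0.50 × 0.20 = 10 points and 0.80 × 0.20 = 16 points.

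**Check in whole participants.** Take 36 per arm, 12 lost in the EA arm, 4 lost in the sham arm, and an assumed true rate of 75% in both. Observed cases are 0.75 × 24 = 18 and 0.75 × 32 = 24.
- Formula as stated: 18/36 = 50% vs 24/36 = 67%, a spurious 17 points in favour of EA.
- Available cases: 18/24 = 75% vs 24/32 = 75%, no difference.
- Missing counted as MoCA below 26: (18 + 12)/36 = 83% vs (24 + 4)/36 = 78%, about 6 points against EA.

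So in this example the choice of rule alone moves the contrast from 17 points in favour of EA to about 6 against it.

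**The case against.** The strongest reply is that the PSCI section gives only a generic formula for an outcome, and that the missing-data rule is where it belongs, in Clinical data analysis. That rule names available cases and covers this outcome; if it governs, lost participants are not counted as PSCI-free. This stands in part. A reader might infer that the protocol has decided to score missing as recovered. It does not say so: it states a formula that has that effect and a second rule that does not, without ranking them. But the formula is explicit about its denominator, so the general rule cannot be assumed to override it.

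A reader might also infer that the error favours EA or reverses the sign of the result. Neither follows. The direction depends on which arm loses more: greater loss in the sham arm would work against EA, greater loss in the EA arm would exaggerate a true benefit, and equal loss only dilutes. Nor is 12 points an expected bias; it needs a 20-point imbalance that the article nowhere predicts.

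A further temptation is to say that the outcome measures persistence and is misnamed, since everyone is below 26 at entry. The Exclusion criteria rule out previous stroke and pre-existing cognitive impairment, so a 3-month case is new relative to the pre-stroke state. The label is defensible.

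Finally, the outcome is exploratory, is one of several secondary outcomes, and does not bear on the sole primary endpoint. That limits the importance of the point. It does not make the estimate correct, and the plan promises effect sizes with 95% confidence intervals for these outcomes.

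**Conclusion.** The point holds. As written, the formula treats a missing 3-month MoCA as absence of PSCI and conflicts with the available-case rule elsewhere in the same article. At the anticipated 20% loss, if it is equal between arms, reported rates fall by a fifth and true differences shrink by a fifth. With unequal loss and no true effect, the arm with more loss gains p × the difference in loss, a range that starts at 0 and reaches 12 points at an assumed 60% and a 20-point imbalance. These sizes rest on loss being unrelated to PSCI status and on assumed rates and splits; only the overall 20% is the article's. If loss does depend on PSCI status, the available-case rate is biased too, which is why a sensitivity analysis is needed alongside the corrected denominator. The primary MoCA analysis is untouched.

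**What to change.** Change the denominator in the PSCI incidence section to randomised participants with a 3-month MoCA, in line with the available-case rule. Alternatively, multiply impute the 3-month MoCA in all randomised participants from baseline and week-4 MoCA, and then dichotomise at 26. State which of the two is the main analysis before allocation is revealed to the analysts. In either case, report the number without a 3-month MoCA in each arm and add one sensitivity analysis that counts missing as MoCA below 26. The outcome need not be renamed. The cost is one corrected sentence plus a short addition to the analysis section; no new data, visits or participants are needed.
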